Indeed, despite evidence of clinical benefits associated with the presence of a primary contact physiotherapist in the ED (effectiveness), scientific evidence remains rather scarce regarding the cost-effectiveness of this model of care. Two studies conducted in primary care settings (primary care clinic and private clinic) report that primary contact physiotherapist management is associated with a slight increase in health-related quality of life and a decrease in total costs compared to usual management by a family physician [30, 31]. In addition, early physiotherapy management was associated with a decrease in total MSKD-related costs for up to two years after initial management [17, 19, 32]. Two cost-minimization studies conducted in Great Britain looked specifically at the costs associated with the integration of a primary contact physiotherapist in the ED compared to usual management by an emergency physician. According to the study by Richardson et al. (2005, n = 766 patients with non-fracture MSKDs), the presence of a primary contact physiotherapist in the ED results in costs equivalent to usual management (emergency physician) [33]. Similarly, according to McClellan et al. (2013, n = 372 patients >16 years of age with a peripheral MSKD), management by a primary contact physiotherapist results in costs at least as high as usual management (emergency physician) [34]. Nevertheless, in addition to having been conducted exclusively in Great Britain several years ago, these two studies only measured the costs of the two models of care compared and not their effectiveness, the authors assuming that the two models compared were equivalent in terms of clinical effectiveness. These studies are thus not considered to be formal economic evaluation according to current guidelines, but rather a costing exercise, in that a cost-effectiveness analysis accounts for the uncertainty associated with the effects of the interventions being compared [35]. To our knowledge, no other study has examined the cost-effectiveness of primary contact physiotherapy in the ED. Furthermore, no study has assessed whether involving primary contact physiotherapists in the ED have a long-term impact on use of health system services and resources for persons with minor MSKDs. Consequently, further evidence is needed on the efficiency of integrating a primary contact physiotherapist in the ED compared to usual management by an emergency physician.

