## Materials and methods

### Study design and costing approaches

This study is composed of three distinct designs, one per objective. The costing approach used for Objective 1 will be Time-Driven Activity-Based Costing (TDABC), which involves determining the per-minute costs associated with each care process included in a care pathway by multiplying the cost per minute of each care process by its duration. Details on this costing approach and its application to the ED have been described by one of the authors elsewhere [36]. Objective 2 will be achieved through a cost-utility analysis approach in which health care costs at the ED visit and those reported at the 1- and 3-month follow-ups will be compiled and combined with the utility scores obtained at the same measurement times, from both Health system and Societal perspectives. Cost-utility analysis is favored in Canada since it uses a generic outcome measure allowing comparison of the health gains associated with several different interventions, such as different models of care [35].

The ICER between the three ED models of care for the management of MSKDs over a two-year period (Objective 3) will be estimated using a cost-effectiveness analysis via a hybrid mathematical model. This model will consist of a decision tree covering the period from the initial ED visit up to three months post-initial visit, and a Markov model starting three months post-initial ED visit and ending 24 months (two years) after the ED visit. The decision tree provides a simple and clear illustration of a patient’s possible short-term care pathways following a new intervention [35, 37]. In addition to reporting the different interventions used, the decision tree also allows for the inclusion of adverse events following the initial intervention, such as a new ED visit for the same condition, and for repeating an intervention over time as needed (e.g., new visit in the ED a few days after the initial visit and then a new visit two months later for the same condition) [35, 37]. It also permits to determine the proportion of disability associated with each of the three ED models of care.

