Of note, the study population for the model of care consisting of primary contact physiotherapist management and discharge from the ED was not observed at all during the pilot pragmatic RCT. Consequently, this model of care will have to be modeled, and therefore cannot be studied in the context of Objectives 1 and 2, which are based on RCT data. All the parameters needed to represent this care model within Objective 3 (probabilities, costs, measures of effectiveness) will be taken from a literature review, an approach regularly used in economic evaluation [44]. However, the studies from which the metrics will be derived will need to have a sample that meets the same inclusion criteria as those presented in Box 1. Data extracted from the literature will be validated with members of the research team and with experts in the field of emergency medicine, MSKDs and rehabilitation if necessary during the construction of the hybrid model [35].

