### Study outcomes

Primary outcomes used to measure the average cost of an ED visit (Objective 1) will be the costs of care processes and the time associated with each care process. This method of costing is routinely used by some members of the research team [36, 45, 46]. The costs related to ED management (medical and non-medical staff, imaging, medication, consumables, maintenance, etc.) were obtained via a formal request made by a member of the research team to the CHU de Québec–UL Finance Department. The time associated with each care process was calculated by a member of the research team using estimates provided by the CHUL medical and non-medical staff that were validated during an observation period in the ED [36, 45]. Uncertainty in measured times will allow the variability of ED costs to be considered, and to derive a distribution of possible costs at baseline for each participant.

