
### Data analysis and interpretation of results

As part of Objective 1, a mapping of the care pathways encountered will be completed for each type of MSKD encountered in our study population (i.e., low back pain, neck pain, upper limb, lower limb) (Fig 1). The unit cost of each of the resources, consumables and indirect costs required in each process of care of the care pathway will be calculated and multiplied by the duration of each process to obtain the cost related to each process of care present in the care pathway. The costs associated with each process will be summed to obtain the total cost of the ED care pathway specific to each MSKD and each model of care (i.e., emergency physician or primary contact physiotherapist and emergency physician management). A generalized linear model with a Gamma distribution and log link will be used to test whether there is a significant difference in the costs of managing equivalent MSKDs between the two models of care [52, 53].

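### In months 0–3 of Objective 3, physiotherapist-alone costs come from publications while the two trial models use local costing, so its incremental cost is confounded with costing source

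*Protocol article*

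**What the plan says.** The Data collection section explains that the physiotherapist-alone model "was not observed at all during the pilot pragmatic RCT" and so has to be modelled. It then sets the rule: "All the parameters needed to represent this care model within Objective 3 (probabilities, costs, measures of effectiveness) will be taken from a literature review". Two controls follow. On eligibility of sources, "the studies from which the metrics will be derived will need to have a sample that meets the same inclusion criteria" as in Box 1. On checking, "Data extracted from the literature will be validated with members of the research team and with experts", the experts being consulted if necessary.

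The two trial models are handled differently. The ED visit is costed by TDABC (Study design and costing approaches). The ED cost inputs, which cover staff, imaging, medication, consumables and maintenance, "were obtained via a formal request made by a member of the research team" to the hospital's finance department (Study outcomes). Process costs are then built up by condition and model: "The costs associated with each process will be summed to obtain the total cost of the ED care pathway specific to each MSKD" (Data analysis and interpretation of results). Follow-up resources to three months are priced from Quebec public repositories and, for physiotherapists and similar professionals, from private-sector hourly rates. The resulting three-month averages feed the Objective 3 decision tree (Study outcomes).

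For months 3–24, Study outcomes takes costs and effectiveness from the literature for all three models.

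**The concern.** An incremental cost is interpretable only if both terms count the same items at the same prices. Here the physiotherapist-alone term would be a published monetary figure, and the term subtracted from it would be a local bottom-up figure. The difference then contains two things: the effect of the care model, and any systematic gap between the two costing sources. Such a gap can come from which items are counted (non-medical staff, maintenance, consumables, indirect costs), from relative wages, and from country and price year.

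Country and price year are a realistic worry on the article's own account. The Introduction names only two cost studies of physiotherapists in the ED and criticises them: "in addition to having been conducted exclusively in Great Britain several years ago, these two studies only measured the costs". It also knows of no other cost-effectiveness study in this setting.

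The stake is the ranking. The project aims to identify the most efficient model, and physiotherapist-alone enters that comparison only through Objective 3. The affected window contains the ED visit itself, which is where the three models differ by design.

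**Working it through.** **Step 1: cost source by model and period**

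| Period | Physician alone; physiotherapist + physician | Physiotherapist alone |
|---|---|---|
| ED visit | Local TDABC, hospital finance rates | Literature |
| Follow-up to month 3 | Quebec repositories, local private-sector rates | Literature |
| Months 3–24 | Literature | Literature |

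The split covers 3/24 = 12.5% of the horizon. The other 21/24 = 87.5% uses one type of source for all models. Duration is not cost share, and the ED visit lies in the first three months.

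**Step 2: do the stated controls remove an offset?**

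- The Box 1 requirement matches patients. It does not match costing method, items counted or prices.
- Validation by the team and experts checks plausibility. It does not re-price a published total.
- Monte Carlo sampling spreads uncertainty around each parameter. It does not remove a systematic gap between sources.
- The three scenarios concern missing utility scores, outliers and the definition of the Markov states. None varies the costing source.

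**Step 3: how large an offset would matter?**

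The plan gives no cost or ICER, so there is no figure to reproduce. The following rests on assumed values only.

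- Comparator's 0–3 month cost = 100.
- True local cost of physiotherapist-alone = 100 + d.
- Published cost = (100 + d)(1 + b), where b is the relative gap between costing sources.
- Artefact = (100 + d) × b. Reported difference = d + artefact.
- Artefact share = |artefact| / (|artefact| + |d|).
- The artefact equals the true difference when |b| = |d| / (100 + d).

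| d | b | Artefact | Reported difference | Artefact share |
|---|---|---|---|---|
| −5 | +10% | 95 × 0.10 = 9.5 | +4.5 (sign reversed) | 9.5/14.5 = 66% |
| −10 | +10% | 90 × 0.10 = 9.0 | −1.0 | 9/19 = 47% |
| −10 | +20% | 90 × 0.20 = 18.0 | +8.0 (sign reversed) | 18/28 = 64% |
| −30 | +10% | 70 × 0.10 = 7.0 | −23.0 | 7/37 = 19% |
| −30 | +30% | 70 × 0.30 = 21.0 | −9.0 | 21/51 = 41% |

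Break-even offsets:

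- d = −5: 5/95 = 5.3%
- d = −10: 10/90 = 11.1%
- d = −20: 20/80 = 25%
- d = −30: 30/70 = 42.9%

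An offset in the opposite direction (b negative) would exaggerate the saving instead of hiding it. A small true difference is fragile and a large one is not. Small differences are plausible here: the Introduction reports that the two British studies found physiotherapist costs equivalent to, or at least as high as, physician care.

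**The case against.** The strongest defence has four parts.

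1. **The article is condensed.** Currency conversion, price year and harmonisation of published costs may be set out in a fuller plan. This stands, and their absence is not part of the point. The point is the rule that is stated: costs themselves come from publications. Conversion would not align the items counted or relative wages.

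2. **The sources are not named.** One British study enrolled patients over 16 with peripheral disorders only, and the other enrolled non-fracture disorders. The target here is ages 18–80 with peripheral or spinal disorders, so either study may fail the Box 1 filter. For medium- and long-term data, the Discussion also allows expert estimates. This stands: a change of country and price year is probable, not certain.

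3. **Some local pricing may be intended.** Public cost repositories are listed as supplementary data for all three objectives, and the pricing paragraph in Study outcomes opens by covering Objectives 2 and 3. That leaves room to read the rule as meaning quantities to be priced locally. The rule's own wording lists costs separately from probabilities and effectiveness, so the text as written does not say so.

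4. **Borrowing from the literature is routine in modelling.** True, and it supports borrowing probabilities and quantities. It does not justify two price systems within one increment.

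A reader might infer two stronger claims. One is that the physiotherapist-alone increment mostly reflects the change of costing source. The documents give no costs, and in the cases tabulated the artefact share runs from 19% to 66%, so this does not follow. The other is that a consistent local figure already exists: the combined-arm pathway with the physician's process removed. That model was never observed, and the subtraction assumes that physiotherapist time, imaging, medication and patient mix are unchanged when no physician follows. Nothing in the article supports that.

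**Conclusion.** The point holds in a limited form. For months 0–3 of Objective 3, the incremental cost of physiotherapist-alone against each trial model is confounded with costing method, and probably with country and price year. No stated control or scenario addresses this. The size cannot be computed from the article. On the assumed scale, an offset of about 5–11% is enough to cancel a true difference of 5–10%, while a true difference of 30% would need about 43%.

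The conclusion rests on reading the Data collection rule as written, with costs meaning monetary costs. It does not extend to months 3–24, where all three models draw on literature, or to Objectives 1 and 2, which do not include this model. It is a cheap improvement to make before the decision tree is populated.

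**What to change.** 1. In Data collection, reword the rule so that the literature supplies only probabilities, process times and resource quantities (imaging, medication, referral, re-visits) for the physiotherapist-alone model in months 0–3. Price these with the same TDABC unit costs and Quebec sources used for the two trial models, and keep shared ED processes identical across models.

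2. Use the combined-arm process map without the physician's process only as a starting structure. State its assumption (unchanged physiotherapist time, imaging, medication and patient mix), replace elements with published quantities where they exist, and vary the rest.

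3. In Data analysis and interpretation of results, add a costing-source scenario to the three listed. Use published monetary costs there, as an external check on the base case.

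The cost is a rewritten rule, one more scenario and modest modelling work. The local rates, the process maps and a physiotherapist hourly rate are already collected or planned. The downside is that published totals without reported quantities cannot be used in the base case, and some quantities may need expert estimates, which should be labelled as such.

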### Study outcomes

Primary outcomes used to measure the average cost of an ED visit (Objective 1) will be the costs of care processes and the time associated with each care process. This method of costing is routinely used by some members of the research team [36, 45, 46]. The costs related to ED management (medical and non-medical staff, imaging, medication, consumables, maintenance, etc.) were obtained via a formal request made by a member of the research team to the CHU de Québec–UL Finance Department. The time associated with each care process was calculated by a member of the research team using estimates provided by the CHUL medical and non-medical staff that were validated during an observation period in the ED [36, 45]. Uncertainty in measured times will allow the variability of ED costs to be considered, and to derive a distribution of possible costs at baseline for each participant.

As part of the cost-utility analysis (Objective 2) and hybrid mathematical model (Objective 3), the efficiency of the ED models of care will be assessed using an incremental cost-effectiveness ratio (ICER). The resulting ICER will be reported in terms of incremental cost per quality-adjusted life years (QALY) gained, between the models of care. The follow-up costs of each participant recorded via the self-administered follow-up questionnaires completed at 1 and 3 months during the pilot pragmatic RCT will be added to the distribution of ED visit costs for each individual obtained under Objective 1. Once all costs have been added, an average will be calculated to obtain an average cost per participant at 3 months, for each model of care (Objective 2 & 3 –decision tree). The questionnaires provided data on resources used by each participant during follow-up such as ED re-visits for the same condition, number of consultations with other health professionals in the public and private sector, imaging tests used, etc. The costs of all resources used in the public healthcare system will be drawn from public cost repositories data from the *Régie de l’assurance-maladie du Québec* (RAMQ) (costs related to the emergency physician and other physicians consulted, drugs, laboratory analysis, imaging tests) [47]. Hourly rates for the primary contact physiotherapist and other health professionals consulted (e.g., massage therapist, chiropractor, osteopath) will be derived from a search of the grey literature and will be based on rates in effect within the private healthcare system, since the majority of these professionals work within this system [47]. Costs related to the use of technical aids (e.g., cane, crutches, walker) will also come from a grey literature search. It should be noted that the salary data available from human resources for all healthcare professionals (physicians and allied health professionals) considered will not allow for variability in hourly costs. The only source of variability considered for the purpose of these analyses will be that related to the time required for ED processes. Utility scores were obtained at the initial visit [48] and at 1 and 3 months using the EQ-5D-5L, a generic standardized questionnaire designed to measure health status in an economic and clinical evaluation [49]. The EQ-5D-5L has been found to be reliable, valid, and sensitive to change [50, 51]. The difference in utility scores between the 3-month follow-up and baseline will be calculated for each participant using area-under-the-curve analyses. Once the difference in utility scores will be calculated for each participant, the differences will be averaged to obtain the average gain or loss in utility scores per ED care model. The mean gain or loss in utility scores will then be transformed into QALYs. The efficiency values and the costs from 3 to 24 months required to run the Markov model (Objective 3) for the three models of care will be taken from the literature.

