### Data collection

Objectives 1, 2 and 3 will be achieved in part using data collected through a two-arm pilot pragmatic randomized clinical trial (RCT) conducted in the ED of the CHUL, one of the five sites of the CHU de Québec—Université Laval (UL) (Quebec City, Canada) from September 2018 to March 2019 (n = 78). This trial aimed to compare the effects of management by a primary contact physiotherapist to usual care provided by an emergency physician for persons presenting with a minor MSKD on their clinical course (pain and pain interference) and the use of resources at ED discharge and after 1 and 3 months post-visit [29]. Two groups of participants were compared: one group managed by a primary contact physiotherapist and an emergency physician and one group managed by an emergency physician alone.

Data were collected at the initial ED visit and at the one- and three-month post-visit follow-ups. While more details of the data collection procedures can be found in our previous paper [29], any person presenting to the ED who met the inclusion and exclusion criteria was seen by a member of the research team who confirmed eligibility, obtained informed consent, and ensured completion of baseline questionnaires. The participant was then randomized to either study group: primary contact physiotherapist + emergency physician management or usual management by the emergency physician alone. After the ED visit was completed, participants were contacted at 1 and 3 months either by phone or email to complete post-visit follow-ups. The supplementary data needed to meet the three Objectives will come from some of the CHU de Québec—UL administrative databases (nominative data: SIURGE (ED management software), Cristal-Net (patient electronic record), and the CHUL’s ED pharmacy transactions directory; administrative data: prescription and over-the-counter drug costs repository), the scientific literature, and public cost repositories (e.g., salaries of general practitioners and specialists, see https://www.msss.gouv.qc.ca/inc/documents/ministere/acces_info/seance-publique/etude-credits-2018-2019/Reponses-aux-questions-generales-et-particulieres-RAMQ.pdf; laboratory analysis costs, see https://publications.msss.gouv.qc.ca/msss/fichiers/2017/17-922-05W.pdf).

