**Fig 3 pone.0277369.g004:**
[figure not shown]
Projected Markov model covering the period from three to 24 months post initial ED visit.

Both the cost-utility analysis (Objective 2) and the hybrid mathematical model (Objective 3) will be conducted from a Health system and a Societal perspective. Results obtained via the EQ-5D-5L at 1 and 3 months (Objective 2 & 3 –decision tree) will be converted to utility scores using the Canadian conversion algorithm developed by Xie et al. [54]. As the 3-month retention rate for the pilot pragmatic trial was 80% [29], some participants’ data are missing (service and resource use, costs, utility scores). Missing data will be imputed using the Missing not at random (MNAR) multiple imputation method [55]. Patient characteristics believed to have influenced loss to follow-up at 1 and 3 months (e.g., socioeconomic status; level of pain and level of catastrophizing at the ED visit) will be examined to identify if they are indeed predictors of loss to follow-up. Characteristics shown to influence follow-up will be used within multiple imputations and within sensitivity analyses regarding these variables. Uncertainty in cost and effectiveness measures for the cost-utility analysis (Objective 2) will be obtained using non-parametric bootstrap resampling with replacement. Uncertainty in the hybrid model parameters (probabilities, costs, and efficiency) (Objective 3) will be obtained via a probabilistic sensitivity analysis performed using a Monte Carlo simulation. Three scenarios will be considered in the probabilistic sensitivity analyses. The first will assume that all participants with missing follow-up data in the control group will have utility scores at 3 months corresponding to those of the 95th percentile, while all those missing in the intervention group will have scores corresponding to those of the 5th percentile. For the second scenario, we will re-analyze all parameters included in the model, excluding outliers. Finally, in the third and last scenario, the different states of the Markov Model will be based not on the level of pain, but on the level of interference of pain on daily activities. Both uncertainties will be represented visually using a cost-effectiveness diagram, cost-effectiveness acceptability curve, and cost-effectiveness acceptability frontier [35]. As there are significant differences between men and women in the strategies used to cope with pain, and the use of health system services and resources during a painful episode (e.g., [56, 57]), subgroup analyses of men and women will be performed for both objectives (p < .05). Subgroup analyses will also be performed according to MSKD category (spine, upper extremity, and lower extremity) for both objectives (p < .05). All the statistical analyses carried out as part of this project and their detailed reporting in scientific publications will adhere to the CHEERS 2022 standard [58].

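### The 3-month incremental cost in Objective 2 is a difference of unadjusted arm averages; this is unbiased, but it gives up a modest amount of precision that baseline data already collected could recover

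*Protocol article*

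**What the plan says.** The Study outcomes section builds the 3-month cost in steps. Each participant's follow-up costs, priced from the 1- and 3-month questionnaires, are added to that person's distribution of ED visit costs. Then "an average will be calculated to obtain an average cost per participant at 3 months, for each model of care". The same average is marked for use in Objective 2 and in the Objective 3 decision tree. On the ratio, the section says: "The resulting ICER will be reported in terms of incremental cost per quality-adjusted life years (QALY) gained, between the models of care". The cost numerator is therefore the difference between two arm averages.

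The Data analysis and interpretation of results section adds imputation of missing data and, for Objective 2, a non-parametric bootstrap. It names no covariate for the 3-month cost comparison. The only regression for costs is placed under Objective 1, the ED visit: "A generalized linear model with a Gamma distribution and log link will be used to test" for a cost difference between the care models for equivalent MSKDs. No baseline covariates are listed for it.

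Baseline values are available. Utility was measured at the initial visit. The "level of pain and level of catastrophizing at the ED visit" are given as examples of possible predictors of loss to follow-up, to be used in imputation and related sensitivity analyses. MSKD category and sex appear as subgroup variables.

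**The concern.** Total cost over three months plausibly depends on how severe the condition was at presentation and on the body region affected. The article itself gives differences between men and women in service use as a reason for subgroup analysis, so it accepts that a baseline characteristic can relate to resource use. In a randomised comparison of this size, prognostic covariates will differ somewhat between arms by chance. An unadjusted difference in mean cost carries that variation as noise. Regression on the same covariates would remove part of it.

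What is at stake is efficiency: a somewhat wider spread of incremental cost than the data require, in a pilot-sized sample, carried into the cost-effectiveness plane, the acceptability curve and the decision-tree cost input. The existing safeguards serve other purposes. Baseline predictors in the imputation model help to fill in missing values but do not adjust the arm contrast among those observed. The bootstrap displays the imprecision but does not reduce it.

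**Working it through.** The article gives no sample-size calculation, cost standard deviation or target difference for Objective 2, so there is no figure to reproduce. The check asks how much precision adjustment could recover.

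**Inputs from the article**
- 78 participants in two arms (Data collection).
- 80% retention at 3 months (Data analysis and interpretation of results): 0.80 × 78 = 62.4, about 62 observed.

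**Assumptions**
- Allocation 1:1, so 78/2 = 39 per arm. The article says only that "The participant was then randomized to either study group". A 40/38 split changes the standard error by 0.03%.
- Share of cost variance explained by the covariates, R²: 0.05, 0.10 and 0.20. The article reports none.
- Four covariate terms: baseline pain, baseline utility, and two indicators for the three MSKD categories used in the subgroup analyses.

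**Step 1: size of chance imbalance.** The SD of the standardised difference in a baseline score is √(2/39) = 0.226. The contribution of covariate imbalance to the cost difference, in cost SDs, is 0.226 × √R²:
- R² = 0.10: 0.226 × 0.316 = 0.072
- R² = 0.20: 0.226 × 0.447 = 0.101

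This contribution is already inside the unadjusted standard error, which is also 0.226 cost SD. It is not an extra error on top.

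**Step 2: precision with 78 analysed.** Residual degrees of freedom fall from 76 to 72. The ratio of adjusted to unadjusted standard error is √[(1 − R²) × 76/72]:
- R² = 0.05: √(0.95 × 1.0556) = 1.001
- R² = 0.10: √(0.90 × 1.0556) = 0.975, a 2.5% reduction; 1/0.975² = 1.05, worth about 5% more patients
- R² = 0.20: √(0.80 × 1.0556) = 0.919, an 8.1% reduction; 1/0.919² = 1.18, worth about 18% more patients

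**Step 3: precision with about 62 observed.** Degrees of freedom fall from 60 to 56. The ratio is √[(1 − R²) × 60/56]:
- R² = 0.05: √(0.95 × 1.0714) = 1.009, a 0.9% loss
- R² = 0.10: √(0.90 × 1.0714) = 0.982, a 1.8% reduction
- R² = 0.20: √(0.80 × 1.0714) = 0.926, a 7.4% reduction

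**Step 4: break-even.** Adjustment pays once (1 − R²) falls below the inverse of the degrees-of-freedom factor: R² above 1 − 72/76 = 0.053 with 78, or above 1 − 56/60 = 0.067 with 62.

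**Step 5: check with skewed costs.** In simulated log-normal costs (39 per arm, 8,000 runs, log-SD 0.8, no true difference, one covariate, linear adjustment), both estimators centred on zero. The adjusted-to-unadjusted SD ratio was 1.01, 0.97, 0.91 and 0.80 at raw-scale correlations of about 0, 0.26, 0.44 and 0.61. A separate simulation of a Gamma log-link model with averaged predictions also showed no visible bias. Its ratios were 0.99 with no prognostic covariate, 0.91 at R² about 0.09 and 0.84 at about 0.16. That case is favourable, because the mean model was correctly specified.

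**The case against.** The strongest reply is that nothing stated is wrong. Under randomisation the difference in arithmetic mean cost is unbiased, and the spread of the planned bootstrap already includes the variation due to chance imbalance. That stands in full; only efficiency remains.

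A second reply is that the sentence on averages only describes how costs are assembled, and that covariates belong in a fuller plan. A fuller document may indeed specify adjustment. But the article does more than stay silent: it sets out summing, averaging per care model, forming the incremental ratio and bootstrapping. Read as written, that is an unadjusted estimator.

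Third, the gain rests on an R² that the article does not supply, and it disappears if the covariates are weak predictors. This also stands. The article further says that results from a pilot trial need caution and acknowledges the small sample, though it ties the latter to tree branches and subgroups.

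Three stronger readings are tempting and are not supported:
- A reader might infer that the plan adjusts for baseline in Objective 1 and abandons this in Objective 2. The Objective 1 Gamma model names no baseline covariates, and with care model alone such a model returns exactly the raw arm means.
- A reader might infer that the two halves of the ICER describe differently balanced groups. The plan specifies no regression adjustment of QALYs. It averages within-person utility differences, which use baseline utility but are not covariate adjustment.
- A reader might infer that adjustment would protect the sign of the incremental cost. At an assumed coefficient of variation of 1 to 2, the unadjusted standard error is 23-45% of mean cost. A 2.5-8% cut leaves it at about 21-22% or 42-44%, too small a change to secure a sign.

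**Conclusion.** The point holds as a minor matter of efficiency. The planned 3-month cost contrast is valid but unadjusted. Adjusting it for values already collected would reduce its standard error by about 2.5-8% with 78 analysed, or about 2-7% with about 62 observed, if the covariates explain 10-20% of cost variance. At 5% explained, the effect runs from nil to a loss of just under 1%. These figures rest on the assumed R², near-equal allocation and four covariate terms. With imputation, the effective sample should lie between the two cases. The article supports no claim of bias or of faulty intervals.

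**What to change.** State in the plan that the 3-month cost difference will be estimated by a pre-specified regression on care model, baseline pain, baseline utility and MSKD category. The Gamma log-link model already named for Objective 1 would serve. Within each imputed data set and bootstrap sample, predict every participant's cost under each of the two care models, average the predictions over all participants, and take the difference. Report the unadjusted arm averages and their difference alongside.

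The change needs no new data. It costs a few degrees of freedom and some reliance on the mean model; the unadjusted result is the check on that reliance. Keep the covariate list this short, because each further term raises the R² needed to break even, and fix it before the cost data are analysed.
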